### Study population

Participating sites include: Hospital Materno Infantil and Hospital General Valladolid, both in Yucatán, México; Hospital Enrique Aguilar Cerrato, La Esperanza in Intibucá, Honduras; Hospital Santa Bárbara in Santa Bárbara, Honduras; and Instituto Maternidad Provincial Nuestra Señora de las Mercedes in Tucumán, Argentina.

All consecutive live births occurring during the defined study period will be included, irrespective of the gestational age or the route of delivery (vaginal or cesarean).

All subjects must meet all of the inclusion criteria to participate in this study.

• *Inclusion criteria***:** Women 18 years old or more, informed consent, live birth.

All subjects meeting any of the exclusion criteria at baseline will be excluded from study participation.

• *Exclusion criteria***:** Women residing outside of the follow-up area.

### Follow-up

Newborns will be followed up at 4–8 weeks and 10 months. In each country, a dedicated team will perform home visits. The follow-up will be done within the following geographical limits: in Mexico, the Yucatan peninsula (i.e., the states of Yucatan, Campeche, and Quintana Roo); in Honduras, the departments of Intibucá and Santa Barbara; and in Argentina, the province of Tucuman. A first home visit will take place at 4–8 weeks postpartum, when parasitological tests will be performed again if the first parasitological examination on cord blood was negative. Those infants with positive tests will be considered infected and referred for treatment. If the newborn has not been discharged from the hospital at four weeks postpartum, the first follow-up visit will be done in the hospital, and the first home visit will be done within four weeks after discharge to collect data on siblings. Those siblings who are not tested during the first home visit will receive a second visit at 10 months postpartum.

The mothers of confirmed infected children and/or mothers who are themselves confirmed as seropositive will be informed and advised to contact their local health provider. Repeated household visits will be performed until follow-up at the health provider is confirmed, and until the treatment of the infant is completed. Every effort will be made to ensure that infants with congenital *T. cruzi* infection identified at birth or at the 4-to-8-week visit are treated by the health providers before the 10-month follow-up visit and that infants diagnosed at the 10-month follow-up visit are also treated without delay. Newborns and infected siblings will be treated according to local standards, which include a course of 30 to 60 days of benznidazole or nifurtimox [2]. In Honduras and Mexico, and in public hospitals in Argentina, the treatment can only be obtained from the Ministry of Health. We will provide each infected subject with a follow-up card, which will be stamped and signed by the health provider at each follow-up visit and when treatment is given. The mother will also be asked to complete the card on a daily basis to indicate when treatment has been given. We will perform household visits every two weeks to confirm treatment. During household visits, we will collect information from the subjects’ cards and take digital pictures (with date and time) of the cards. We will also register the number of doses of benznidazole or nifurtimox made available to the subject and take digital pictures (with date and time) of the drug supply available in the household.

Geographic data will be collected for vector risk analysis. Street addresses are often unreliable in the areas where participating women live; thus, detailed information will be collected at enrollment. During the first home visit, considerable effort will be made to locate the household, involving key informants if needed. Once located, we will use handheld computers with GPS to map the location of the household. We will use established procedures and software developed by the Centers for Disease Control and Prevention (CDC) [21]. The latitude and longitude of the main entrance are determined after obtaining the appropriate GPS signal, and additional characteristics of the household are noted. The sampling procedures included in the CDC software are not needed here, but the system allows us to navigate back to the household for return visits*.* In addition, these GPS coordinates will be entered into a GIS database (ArcView Geographic Information Systems [ArcGIS] software 9.3, Environmental Systems Research Institute, Redlands, CA) to produce maps of the geographic distribution of seropositive cases. These maps will be used to estimate vectorial exposure in the households from the seropositive cases.

### Entomological data

Entomological data will be obtained from two different sources to estimate vectorial exposure in the households from seropositive mothers. First, we will use vector distribution and house infestation data from the respective vector surveillance and control programs in Argentina and Honduras, which provide geocoded information and maps on the presence of vectors of different species at the village/locality level. For each household of a seropositive mother, we will thus determine if it is located in a village with or without known house infestation by triatomines using cumulated vector data from the past five years. For the Yucatan Peninsula, Mexico, in the absence of vector control programs, we will use published entomologic risk maps [22]. Based on these maps, households located in villages with low or absent risk will be classified as without house infestation, and households from villages with medium or high risk will be classified as with house infestation.

Second, we will use the community participation method, which was successfully piloted in and previously used in Argentina as well [23]. All of the households from seropositive mothers will be included, corresponding to an estimated 100 households in Mexico, 300 in Honduras, and 200 in Argentina. During the first household visit, information on Chagas’ disease and triatomines will be provided, including photographs and the display of dried specimens of the vector, to ensure that study participants will recognize the vector. Participants will then be instructed to collect any triatomines observed inside (domestic) or outside (peri-domestic) of their homes using a safe procedure and to place them into separate labeled plastic vials or bags. Any insects captured since the time of the initial visit will be gathered during the second visit at 10 months. Triatomine species will be identified by local entomologists from vector control programs in Argentina and Honduras and by entomologist researchers in Mexico, using established entomological keys [24,25].

Because vector control is well underway in Argentina and Honduras, we expect house infestation by triatomines to be limited in these countries, while triatomine collections in Mexico will be much more important. Based on these collections, each household will be classified as infested or non-infested, and infested households will be considered at risk of vectorial transmission, irrespective of the *T. cruzi* infection status of the bugs. *T. cruzi* infection status in triatomines will not be determined at this stage, as it is highly unlikely that a sufficient sample size may be reached to determine significant differences in infection rates and *T. cruzi* transmission risk between households. However, all collected insects will be stored in ethanol for subsequent analysis and PCR diagnostic of infection if needed [26,27].

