– 2. To compare the *T. cruzi* infected mothers’ characteristics and exposure to vectors in regions where TcI is predominant and regions where Non-TcI is predominant; and

– 3. To describe the birth outcomes of infected and uninfected infants born to TcI and Non-TcI seropositive women.

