### Variables

The exposure to TcI will be defined by *T. cruzi* genotyping showing TcI on maternal blood and/or cord blood. In the absence of successful *T. cruzi* genotyping on maternal or cord blood, births occurring in Mexico or Honduras will be considered exposed to TcI.

The exposure to Non-TcI will be defined by *T. cruzi* genotyping showing Non-TcI on maternal blood and/or cord blood. In the absence of successful *T. cruzi* genotyping on maternal or cord blood, births occurring in Argentina will be considered exposed to Non-TcI.

The exposure to both TcI and Non-TcI (co-infection) will be defined by *T. cruzi* genotyping of both TcI and Non-TcI on maternal blood and/or on cord blood, or of TcI on maternal blood and Non-TcI on cord blood, or of Non-TcI on maternal blood and TcI on cord blood.

The primary outcome (Specific Aim 1) will be the congenital *T. cruzi* infection, which will be defined as the presence of one or more of the following criteria:

– Presence of parasites in cord blood (direct parasitological microscopic examination); and/or

– Presence of parasites in infant’s blood at 4–8 weeks (direct parasitological microscopic examination); and/or

– Persistence of *T. cruzi*-specific antibodies at 10 months, as measured by two tests.

A seropositive mother will have at least one positive rapid test on cord blood and a positive ELISA on maternal blood.

The mothers’ characteristics and exposure to vectors variables (Specific Aim 2) that will be collected include:

– Maternal age;

– Parity (including current birth);

– Infected sibling (yes/no) (siblings previously treated for *T. cruzi* infection will be presumed as having been infected);

– Maternal parasitic DNA amount;

– HIV serology (according to tests performed routinely in each country);

– Presence of vectors in the household (Infestation) (yes/no).

– Location in an area with risk of vectorial transmission (yes/no)

The birth outcomes (Specific Aim 3) to be measured are the following:

– Premature rupture of the membranes (PROM), defined as rupture of membranes before admission or before the onset of contractions, whatever the timing of the rupture; [14]

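### The village-level vector variable is defined differently in Mexico than in Argentina and Honduras, so Aim 2's regional comparison of vector exposure partly compares definitions, with a bias of unknown size and sign

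*Protocol article*

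**What the plan says.** Aim 2 (Background) sets out to compare infected mothers' "characteristics and exposure to vectors in regions where TcI is predominant and regions where Non-TcI is predominant". The Variables section lists two vector items under this aim: vectors in the household, and location in an area at risk of vectorial transmission.

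The Entomological data section gives two sources.

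- **Village level, Argentina and Honduras.** Programme data decide whether the household is "located in a village with or without known house infestation by triatomines using cumulated vector data from the past five years".
- **Village level, Yucatan Peninsula.** There is no control programme, so published risk maps are used. On these, "households located in villages with low or absent risk will be classified as without house infestation". Only a medium or high grade makes a household count as infested.
- **Household level, all three countries.** Residents collect triatomines between the first home visit and the 10-month visit, and each household is classed as infested or not.

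The Analysis plan uses area location again in its second-step, more conservative transmission analysis. There, location in an at-risk area is by itself enough to meet the vector part of the exclusion rule.

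**The concern.** The two village rules are not equivalent. One asks whether any infestation has been recorded over five years. The other applies a cut-off to a mapped grade and puts low risk together with absent risk. The protocol itself separates low from absent, so low is not zero, yet both are coded as unexposed.

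The rule follows country, and country defines the comparison groups when Aim 2 compares regions. All Mexican households are on the TcI side, and Argentina is the whole Non-TcI side. Neither a larger sample nor adjustment can separate exposure from definition for Mexico. A regional difference in this variable, or its absence, could not be attributed to exposure alone.

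The same applies to the conservative analysis under Aim 1. Infants in Mexican low-risk villages would be kept, while infants in Argentine or Honduran villages with any recorded infestation would meet the vector criterion.

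**Working it through.** **Reading assumed.** The village-level source is taken to feed the area-location item, and the household collection to feed the household-vector item. The article labels the village result as house infestation but does not state this link outright.

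**Step 1: weights.** The Entomological data section expects 100 households in Mexico, 300 in Honduras and 200 in Argentina. The Sample size section reproduces these:

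- Honduras: 7,500 × 4% = 300.
- Argentina: 10,000 × 2% = 200.
- Mexico: 13,000 × 0.4% to 1% = 52 to 130, which contains 100.
- Total: 100 + 300 + 200 = 600, as planned.

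Mexico's weight in the TcI region is 100/400 = 25%. At the ends of its range it is 52/352 = 15% and 130/430 = 30%.

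**Step 2: effect of the Mexican cut-off.** Let L be the share of Mexican households in low-risk villages. Let f be the share of those that would be exposed under the Argentina/Honduras rule. The documents give neither, so both are assumptions. Moving low-risk villages to the common rule shifts the TcI-region share by 0.25 × L × f.

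| L | f | Shift, Mexico alone (L × f) | Shift, TcI region |
|---|---|---|---|
| 0.2 | 0.5 | 10 points | 2.5 points |
| 0.4 | 0.5 | 20 points | 5 points |
| 0.4 | 1 | 40 points | 10 points |
| 0.6 | 1 | 60 points | 15 points |

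The ceiling for the TcI region is 25 points. The Honduras–Argentina contrast does not move.

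**Step 3: can it hide or reverse a difference?** Assume 20% exposed in both Honduras and Argentina.

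- *Hidden.* Mexico medium/high 20%, L = 0.4, f = 0.5. Protocol rule: (100 × 0.20 + 300 × 0.20)/400 = 20%, a difference of 0. Common rule: Mexico 20% + 20% = 40%, so (40 + 60)/400 = 25%, a difference of +5.0 points.
- *Reversed.* Mexico medium/high 10%, L = 0.6, f = 0.5. Protocol rule: (10 + 60)/400 = 17.5%, a difference of −2.5 points. Common rule: Mexico 10% + 30% = 40%, so 25%, a difference of +5.0 points.

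**Step 4: adding the five-year window.** Assume that 30% of Mexican households are in villages with vectors now and that 30–60% of these are in villages graded low. Mexico then measures 30% × 0.7 = 21% down to 30% × 0.4 = 12%. Assume that 5% of villages in Argentina and Honduras have a detected infestation in any one year, and treat village shares as household shares.

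- Current exposure: 0.25 × 30% + 0.75 × 5% = 11.25% against 5%, a difference of +6.25 points.
- Measured, if years are independent: the five-year figure is 1 − 0.95^5 = 22.6%. The TcI region is 0.25 × (12 to 21%) + 0.75 × 22.6% = 20.0–22.2%, against 22.6%, a difference of −2.7 to −0.4 points.
- Measured, if the same villages are infested every year: the five-year figure stays at 5%. The TcI region is 6.75–9.0%, against 5%, a difference of +1.75 to +4.0 points.

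**Step 5: sign.** Step 2 moves Mexico in one direction only. Let M be the share of Mexican households in medium- or high-risk villages, and g the share of those with no infestation that programme data would have recorded. The net shift is then 0.25 × (L × f − M × g), which is negative whenever M × g exceeds L × f. The documents do not fix any of these four quantities.

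**The case against.** The different source is disclosed and forced by the lack of a Mexican control programme. A uniform household measure covering all seropositive mothers is already planned. The confounder list in the Analysis plan uses household vectors, not area location. No pooled test of the area variable is spelled out, and country-level tables are the kind of detail an article leaves to fuller documents. All of this stands, and it limits the damage. It does not remove it: the article itself fixes the two rules, lists area location under Aim 2 and uses it in an exclusion. The missing programme explains the different source but not the choice to pool low with absent.

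A reader might infer a stronger claim: that the rules err in opposite directions, overstating Argentina and Honduras and understating Mexico. The documents do not support this. A map may grade a village medium or high without any recorded infestation, and programme data can miss villages never searched. What the grades mean and what period they cover depends on a cited source that is not at hand.

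Nor does the expectation that "we expect house infestation by triatomines to be limited in these countries, while triatomine collections in Mexico will be much more important" settle the direction. It introduces the household collections and makes no specific prediction for the village-level variable.

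**Conclusion.** The point holds in a limited form. One yes/no variable is built from two non-equivalent rules tied to country. The Aim 2 regional contrast on that variable is therefore partly a contrast of definitions, and the conservative transmission analysis excludes by a different standard in Mexico.

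The size and sign of the bias cannot be determined from the documents. With Mexico at about 25% of TcI-region households, the low-risk coding can move the regional share by at most 25 points, and by 2.5 to 15 points in the assumed examples. Attenuation, masking and reversal of a small true difference are all possible, but none is demonstrated.

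It would be tempting to set Mexico alone (12–21%) against Argentina (23%) and conclude that a large true contrast of 30% against 5% is reversed. That is not the Aim 2 comparison, which includes Honduras. Reversal under those inputs also requires infestation to be independent from year to year; if the same villages persist, the direction is kept. The household measure and the Honduras–Argentina contrast are not affected by the differing village rules. The issue concerns a secondary aim and a secondary analysis, and it is worth correcting because correction is cheap.

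**What to change.** 1. State that the cross-region comparison of vector exposure in Aim 2 rests on the household triatomine collection, which uses one method in all three countries.
2. Report the area variable by country, with Honduras against Argentina as the like-for-like contrast, and explain that the Mexican figure is built on another rule.
3. Add a sensitivity analysis that counts Mexican low-risk villages as exposed, leaving only absent-risk villages unexposed. Apply it both to Aim 2 and to the area-at-risk exclusion in the second-step transmission analysis.

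The five-year window in Argentina and Honduras need not change. Earlier exposure may be relevant for mothers who are already infected, so restricting to the latest year would be a matter of preference.

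The cost is some rewording and recoding of data already in hand. The drawback is that household collection data will be missing for families not reached at 10 months. On the plan's own estimate of under 10% loss, that is fewer than 0.10 × 600 = 60 households.

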### Blood samples and laboratory evaluations

Immediately after the clamping and sectioning of the umbilical cord, 20 ml of venous umbilical cord blood will be collected from the placental side of the cord with a needle and syringe and placed in EDTA (15 ml) and heparinized (5 ml) tubes following an established protocol. After obtaining informed consent, rapid serological tests will be performed on cord blood within the next six hours. If both rapid serological tests are negative, the mother will be excluded from the study and we will select a randomized sample of the umbilical cord blood samples to be stored.

If one of the cord blood rapid serological tests is positive, parasitological examinations will be performed immediately, and samples will be stored for further testing (10 ml on EDTA will be stored for molecular testing and 5 ml for further serological testing). 15 ml of venous maternal blood will be collected in EDTA tubes from mothers and also stored (10 ml for molecular testing and 5 ml for further serological testing).

The samples to be stored for further molecular testing will be immediately mixed with the same volume of guanidine-HCl 6M, EDTA 0.1 M (pH 8), and kept at 4°C until processed. This standard blood treatment contributes to the stabilization of the sample’s DNA content and improves its long-term conservation as well as favors the parasitic DNA dispersion into the entire sample. Blood samples for further serological tests will be stored in part on filter paper kept at 4°C until use, and additional plasma samples will be frozen at -20°C until use.

During the 4-to-8-week follow-up household visits, 2 ml of blood will be collected in heparinized tubes from the infant by venipuncture, or 6 heparinized capillary tubes will be collected by heel stick and transported to the laboratory in mobile refrigerators for parasitological examination within a maximum of six hours. In those cases in which it is not possible to collect enough blood to fill 6 capillary tubes, collecting a blood sample large enough to fill one capillary tube will be considered acceptable. Finger pricks will be used for siblings. A half drop of blood (10 μl) will be collected from the finger with a disposable pipette for the rapid serological test. An additional 100 μl (5 drops) of blood will be stored on filter paper for ELISA study.

During the 10-month household visit, 3 ml of blood will be collected in EDTA tubes from the infant by venipuncture and transported to the laboratory in mobile refrigerators. Rapid tests will be performed, and blood will be stored for further testing (filter paper at 4°C and plasma at -20°C). In those cases in which venipuncture cannot be performed, we will collect blood by heel prick or digital puncture in an Eppendorf (or equivalent) EDTA tube to perform rapid tests and further testing, and one filter paper for ELISA testing will be considered an acceptable minimum.

The member of the follow up team who will perform the venipunctures will be a certified phlebotomist. We estimate that less than 1% of the samples will be unusable. Table 1 summarizes the blood samples to be collected and analyzed.

**Table 1 T1:** Procedures with blood samples

**Time of extraction**	**Source**	**Blood sample**	**Tests to perform**	**Storage requirements**
Birth	Umbilical cord	15 ml EDTA	Stat-Pak.	-
			T. Detect,	
			ELISA*,	Filter paper 4°C, Plasma -20°C*
			PCR*	10 ml Guanidine 4°C*
	Umbilical cord	5 ml heparinized	Parasitological examination*	Max 6 hours at 4°C
Before hospital discharge*	Maternal, venous in all (+) subjects	15 ml EDTA	Stat-Pak,	-
			T. Detect,	
			ELISA,	Filter paper 4°C, Plasma -20°C,
			PCR	10 ml Guanidine 4°C
Follow-up visit at 4–8 weeks after birth*	Infant, venous, or heel stick	2 ml heparinized, 6 capillary tubes (ideally), or at least one capillary tube	Parasitological examination	Max 6 hours at 4°C
	Siblings, finger prick	10 μl	Stat-Pak	-
		100 μl	ELISA	Filter paper 4°C
Follow-up visit at 10 months after birth*	Infant, venous or heel stick or digital puncture	3 ml EDTA, or at least one Eppendorf EDTA tube and one filter paper	Stat-Pak,	-
			T. Detect,	
			ELISA	Filter paper 4°C, Plasma -20°C

*If at least one rapid test on cord blood is positive.

We will use the Chagas Stat-Pak, a rapid immunochromatographic screening test for detection of anti-*T. cruzi* antibodies in whole blood [28,29]. We validated its use on cord blood in the three countries in which we are working [30]. A WHO comparative evaluation also found 94% sensitivity for the Stat-Pak [31]. Other studies have reported similar results in Bolivia [32-34], but a lower sensitivity in Peru [33]. A half drop of blood (10 μl) is collected with a disposable pipette and placed on the rapid test cassette, and buffer is added. The presence of anti-*T. cruzi* antibodies in the sample produces a pink/purple line (positive result) in the reactive area, whereas no line appears in the absence of the antibodies (negative result). A second pink/purple line in the control area confirms that the reaction was completed and that the test is validated. Reading the results in the appropriate area of the device is performed by recording the absence of any line as negative or a strong or weak line as positive. All Stat-Pak results have to be read within 15 minutes. Digital pictures (with date and time) are taken at the 15-minute mark to document the reading.

In addition to the Chagas Stat-Pak, we will use Trypanosoma Detect (T. Detect) rapid immunochromatographic screening tests (InBios, Seattle, Washington), for detection of anti-*T. cruzi* antibodies in whole blood. T. Detect has a 99% sensitivity and specificity compared to consensus panel sera [35]. The test will be performed according to the manufacturer’s instructions. Briefly, 20 μl of whole blood is added to the test strip. Three drops of chase buffer solution are added into a test tube or assay well where the test strip is placed. All T. Detect results have to be read in 10 minutes. The test is positive when both a control line and test line appear. Digital pictures are taken at the 10-minute mark to document the reading.

Blood stored on filter paper and plasma samples will be analyzed using a commercial ELISA prepared with recombinant *T. cruzi* antigens (Chagatest ELISA recombinant, version 3.0, Wiener Laboratories, Rosario, Argentina), according to the manufacturer protocol. Spots of blood will be punched from the filter paper, eluted in the laboratory, and centrifuged and analyzed. The use of filter paper for ELISA has been previously described [36,37].

A confirmatory ELISA will be performed for all 10-month follow-up tests that are positive or in question. The samples will be sent to Tulane University. Serologic analysis will be performed according to the manufacturer protocol using the FDA-cleared Hemagen Chagas Kit (Hemagen Diagnostics, Inc., Columbia, Maryland), a qualitative ELISA designed for the detection of circulating antibodies to *T. cruzi* in serum and plasma.

Congenital infection with *T. cruzi* is sought for by direct microscopic examination of blood buffy coat collected in six centrifuged microhematocrit heparinized tubes as previously described [2,14,38,39]. In those cases in which it is not possible to collect enough blood to fill 6 capillary tubes, collecting blood to fill at least one capillary tube will be considered acceptable. The detection limit of such parasitological detection was estimated to be 40 parasites/ml (p/ml) [38,39], which allowed the detection of more than 90% of the congenital cases in Bolivian endemic areas [40]. The number of positive microhematocrit tubes containing parasites, as well as the number of detected parasites per tube, allowed estimation of parasitemia as either low (≥ 40 p/ml - < 150 p/ml), medium (≥ 150 p/ml - ≤ 400 p/ml), or high (> 400 p/ml). Positive parasitological examinations will be filmed when possible. The films will be downloaded to the Chagas study webpage and shared between the study sites.

We will perform molecular tests to estimate the parasitic DNA amount (PCR followed by a qPCR in positive cases) and to identify the *T. cruzi* genotype (TcI and/or Non-TcI) on the blood of infected mothers. We will also perform PCR followed by genotyping on the umbilical cord blood samples. An international consensus has recognized direct parasitological examinations of cord or neonatal blood collected in capillary tubes, as well as serological investigations of infant blood at 10 months of age, as the best tools for the biological diagnosis of *T. cruzi* congenital infection, whereas PCR must still be standardized and validated for such use [2]. Thus, the research team is using blood parasitological examinations and late serology to identify infected newborns. PCR will not be used for diagnostic purposes, but it will aid in verifying the presence of parasitic DNA in samples before they are quantified via qPCR or before genotyping.

